#### Data analyses

2.8.2

All statistical analyses will be performed by qualified statisticians in SPSS software (SPSS Inc., Chicago, IL, USA; version 13.0) based on the intention to treat (ITT) principle. The data will also be collected and analyzed according to said principle. Continuous variables will be expressed as mean ± SD and compared using unpaired independent *t* tests. Chi-square tests will be used to compare the categorical data between groups.

A two-sided *p* < 0.05 will be considered significant. The trends of change over time in degree of OM, each scale/item of the EORTC QLQ-H&N35 and EORTC QLQ-C30, will be compared between groups with the generalized estimating equation (GEE) in SAS software version 9.4.

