### Randomization and allocation

2.4

By permuted stratified block randomization (block size 4), patients will be randomly assigned to the control group or intervention group in a ratio of 1:1. Stratification factors will include the type of RT (curative/adjuvant) and the application of concurrent chemotherapy (yes/no). A random number generator based on permutation block design will be used to generate randomized sequences for each stratum separately. The random assignment of each participant will be determined before the intervention. To avoid selection bias, the concealed allocation method will use consecutively numbered opaque sealed envelopes.

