### Assessments

2.7

Each patient will participate in the study for at least 6 weeks, starting from the beginning of RT. Demographic and clinical characteristics recorded at baseline will include gender, age, primary tumor location and stage, scheduled treatment, RT dose, and Karnofsky score. Eligible patients will be randomly assigned to the radiology department for functional assessment and intervention.

The study outcomes will be assessed at baseline (2 weeks pre-RT, t0); at the beginning of RT (t1); at 1 (t2), 2 (t3), 3 (t4), 4 (t5), and 5 (t6) weeks; at the end of RT (t7); and at 2 weeks after completion of RT (t8). The schedule of enrollment is shown in Table 2.

**Table 2 tbl2:** Summary of collected data at each time point according to SPIRIT 2013 guidelines.

Period week	Enrollment	Allocation	Treatment						Follow-up
	Week −2	Week 0	Week 1	Week 2	Week 3	Week 4	Week 5	Week 6	Week 8

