#### Sample size

2.8.1

The sample size estimation was based on the mean difference in the change of the OM intensity from baseline. Based on a previous study, we made the following assumptions in calculating the sample size: a mean difference of 0.9 between the two groups, SD of total score of 0.7, a ratio of 1:1 between the two groups, a two-sided significance level of 0.025 and a power of 0.9 [10]. With these assumptions, a minimum sample size of 34 patients (17 patients in each group) is needed. Considering the estimated 15% dropout rate, the estimated sample size is 40 patients (20 patients per group).

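### Randomisation is stratified by RT type and concurrent chemotherapy, but the named t and chi-square tests ignore both factors; if the factors are prognostic, the t test is conservative and precision is forgone

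*Protocol article*

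**What the plan says.** **Allocation (section 2.4, Randomization and allocation).** "By permuted stratified block randomization (block size 4), patients will be randomly assigned to the control group or intervention group in a ratio of 1:1". The strata are named: "Stratification factors will include the type of RT (curative/adjuvant) and the application of concurrent chemotherapy (yes/no"). That makes two binary factors and four strata.

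**Analysis (section 2.8.2, Data analyses).** For continuous outcomes: "Continuous variables will be expressed as mean ± SD and compared using unpaired independent *t* tests". For categorical outcomes: "Chi-square tests will be used to compare the categorical data between groups". The threshold is set by "A two-sided *p* < 0.05 will be considered significant". No stratified or covariate-adjusted comparison is mentioned anywhere in the article.

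The same section adds a longitudinal model. Trends in degree of OM and in the two EORTC questionnaires "will be compared between groups with the generalized estimating equation (GEE) in SAS software version 9.4". Its covariates are not listed. VAS pain, which section 2.7.1 makes a primary outcome, is not among the outcomes assigned to it.

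**Baseline (section 2.7, Assessments).** "The study outcomes will be assessed at baseline (2 weeks pre-RT, t0); at the beginning of RT (t1"), followed by later visits up to two weeks after RT.

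**The concern.** Stratified blocking holds the arms nearly balanced on RT type and chemotherapy, so differences between strata contribute almost nothing to the variability of the treatment contrast. An unpaired t test still counts those differences as noise. If the factors matter for mucositis, the reported standard error exceeds the real one, intervals are too wide and the test rejects too rarely.

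A prognostic role is plausible from the protocol itself. Section 2.5 describes cisplatin as a radio-sensitiser, the Introduction links OM to RT with or without chemotherapy, and the designers chose these factors for stratification. No figure for their prognostic strength is given.

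Pain is the most exposed outcome. It is primary, it is not on the GEE list, and so the t test is the only method named that covers it. The sample size was calculated for OM intensity alone, so pain and quality of life have no stated power that could absorb a loss of precision.

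**Working it through.** **1. Reproduce the plan's sample size.** Inputs from section 2.8.1: difference 0.9, SD 0.7, 1:1 allocation, and "a two-sided significance level of 0.025 and a power of 0.9".

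- Normal approximation: n per arm = 2 × (2.241 + 1.282)² × (0.7/0.9)² = 15.02, rounded up to 16, or 32 in total.
- Noncentral t: power is 0.893 at 16 per arm and 0.913 at 17 per arm, so 17 per arm and 34 in total, as stated.
- Dropout: 34 / 0.85 = 40, as stated.

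The plan's figure is therefore that of an unadjusted two-group comparison. It takes no credit for the stratification.

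**2. Large-sample formula for the mismatch.** Let R² be the share of outcome variance explained by the two factors. With the arms balanced within strata, the real standard error of the difference is the reported one times √(1 − R²). Hence:

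- ratio of unadjusted to adjusted standard error = 1/√(1 − R²);
- true type I error of the t test = 2 × [1 − Φ(1.960/√(1 − R²))];
- for an effect giving 80% power by the unadjusted formula, unadjusted power = Φ(0.842/√(1 − R²)) and adjusted power = Φ(2.802/√(1 − R²) − 1.960).

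With 100 per arm, as in the abstract, that effect is (1.960 + 0.842) × √(2/100) = 0.396 SD. Both R² and this effect are assumptions; neither is in the protocol.

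| R² | SE ratio | True type I error | Power, unadjusted | Power, adjusted |
|---|---|---|---|---|
| 0 | 1.00 | 0.050 | 0.800 | 0.800 |
| 0.1 | 1.05 | 0.039 | 0.813 | 0.840 |
| 0.2 | 1.12 | 0.028 | 0.827 | 0.879 |
| 0.3 | 1.20 | 0.019 | 0.843 | 0.918 |

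**3. Simulation with the actual allocation scheme.** 10,000 trials per setting, blocks of 4 in four strata, N = 200, assumed factor prevalences of 40% and 60%. The t test is compared with a linear model containing arm and the two factors.

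| R² | Type I, unadjusted | Type I, adjusted | Power, unadjusted | Power, adjusted |
|---|---|---|---|---|
| 0 | 0.053 | 0.053 | 0.797 | 0.796 |
| 0.1 | 0.036 | 0.047 | 0.801 | 0.829 |
| 0.2 | 0.030 | 0.054 | 0.822 | 0.878 |
| 0.3 | 0.020 | 0.048 | 0.838 | 0.917 |

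Formula and simulation agree: about 3, 5 and 8 points of power for R² of 0.1, 0.2 and 0.3.

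**4. Effect on the planned power.** Same simulation at N = 34, alpha 0.025, and the planned effect of 0.9/0.7 = 1.29 SD. For R² of 0, 0.1, 0.2 and 0.3:

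- unadjusted power: 0.914, 0.922, 0.930, 0.939;
- adjusted power: 0.911, 0.939, 0.962, 0.979.

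The unadjusted test stays above the planned 0.90 throughout.

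**5. Baseline adjustment.** ANCOVA multiplies the variance by 1 − ρ², where ρ is the baseline-to-outcome correlation. At an assumed ρ = 0.5 this is 0.75, a 25% reduction. A change score has relative variance 2(1 − ρ) = 1 at that correlation, so a t test on changes would not recover the gain. The protocol gives no ρ.

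**The case against.** **Planned power is not lost.** A reader might infer that the trial throws away power it has already paid for. The protocol does not support that: the sample size is itself that of an unadjusted comparison, and the t test meets it (steps 1 and 4). What is forgone is extra precision. This objection stands.

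**The loss is conditional.** The protocol gives no R², and at R² = 0 the two analyses are equivalent. This also stands, which is why the result is given as a range.

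**The GEE may be adjusted.** Its covariates are unstated, and a condensed article may leave them to the full protocol or analysis plan. Silence there is not an error, so the mismatch is established for the t and chi-square tests only. Those tests, however, are expressly named, so the point does not rest on silence.

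**The baseline argument is weaker for pain.** The VAS is described as measuring mucositis pain, and eligibility requires no history of oral ulcer, so values before RT may be near zero and ρ low. Table 2 has no pain row and starts OM intensity at Week 1, so it is uncertain whether a baseline VAS will exist. Nor is baseline ignored altogether: the sample size refers to change in OM intensity, and weight change is an outcome. For pain, therefore, no particular gain from baseline adjustment can be claimed.

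**Categorical outcomes.** All the figures above are for continuous outcomes. Covariate-adjusted logistic regression need not narrow the interval on the log-odds scale, and it targets a conditional odds ratio. No precision gain is claimed here; the case for a stratified test is consistency with the allocation.

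**Conclusion.** The mismatch is real: allocation uses two stratification factors, and the named t and chi-square tests use neither. For continuous outcomes its consequence runs in one direction. If the factors explain 10 to 30% of outcome variance, the t test's standard error is about 5 to 20% too large, its true type I error is about 0.04 to 0.02 instead of 0.05, and about 3 to 8 points of power are forgone at N = 200 for an effect of 0.396 SD. These sizes rest on the assumed R², effect and factor prevalences.

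The mismatch does not bias the estimate, does not inflate false positives and does not endanger the planned 90% power for OM intensity. It is an inexpensive improvement worth making, not a threat to validity. The conclusion does not depend on whether the target is 40 or 200 patients, or on whether alpha is 0.025 or 0.05; those discrepancies are separate points.

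**What to change.** Amend section 2.8.2 before the data are analysed:

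- Compare continuous outcomes with a linear model containing arm, RT type and concurrent chemotherapy, plus the outcome's baseline value where it is measured.
- Compare categorical outcomes with a Cochran-Mantel-Haenszel test stratified by the same two factors.
- State that both factors enter every GEE model, and add VAS pain to the outcomes analysed by GEE.
- Keep the unadjusted t and chi-square tests as sensitivity analyses.
- State whether VAS pain is recorded before RT, so that it is clear whether a baseline covariate is available.

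The cost is a few sentences of analysis text and a few lines of code. The factors are already known for every patient at randomisation, so no new data, visits or patients are needed.

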As noted, patients in the experimental group will be administered medicine in the TCM clinic and receive the TCM preparation from the first week of RT through the end of RT, or for at least 6 weeks during RT. Taking less than 70% of the study medication during the trial period will be considered non-compliance, and patients meeting this criterion will be excluded from the trial. Patients will be evaluated in the oncology and radiotherapy departments every day (except on weekends) for evaluation of mucositis, oral pain, and lesion. Such assessment is possible due to chemotherapy and RT treatment schedule. Patients will record in a diary the manner of the CHM formula administration, schedules, concomitant use with other medications and reports of adverse effects.

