#### Primary outcome

2.7.1

The primary outcome used in this study will be the onset of OM, intensity of OM and pain. After the start of RT, the patients will be examined daily until onset of OM. Once OM presents, the onset will be recorded in the proforma, and thereafter the degree will be examined weekly until RT is completed and then at 2-weeks post-RT by oncologists.

Subjective assessment of mucositis pain will be performed with a 100-mm visual analog scale (VAS, where 0 = no pain and 100 = worst possible pain) [17], and objective OM grading will be conducted according to the Common Terminology Criteria for Adverse Events, version 5.0 (CTCAE v5.0). The CTCAE v5.0 grades of OM are defined as follows: grade 0, no mucositis; grade 1, asymptomatic or mild symptoms with no intervention indicated; grade 2, moderate pain that does not interfere with oral intake or cause diet adjustment; grade 3, severe pain that interferes with oral administration; grade 4, indication of life-threatening consequences and emergency intervention; and grade 5, death [18].

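### Onset of OM is a primary outcome watched for daily, but no test named in the analysis section handles patients without an observed onset

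*Protocol article*

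**What the plan says.** Primary outcome section: "The primary outcome used in this study will be the onset of OM, intensity of OM and pain". On how onset is observed: "After the start of RT, the patients will be examined daily until onset of OM", and then "Once OM presents, the onset will be recorded in the proforma, and thereafter the degree will be examined weekly until RT is completed", with a further grading two weeks after RT. The Interventions section qualifies the daily examination: "Patients will be evaluated in the oncology and radiotherapy departments every day (except on weekends) for evaluation of mucositis, oral pain, and lesion".

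The Data analyses section names three methods under an intention-to-treat heading. Continuous variables get unpaired t tests. For the rest, "Chi-square tests will be used to compare the categorical data between groups". A GEE compares trends in OM degree and in the two EORTC questionnaires. Onset is not among the outcomes given to the GEE.

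Several provisions mean that some patients will have no observed onset. The Sample size section expects 15% dropout, and withdrawal is free at any time. Observation ends two weeks after RT. The Interventions section removes from the trial anyone who takes under 70% of the study medication, and only the ZYLGS arm takes it.

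**The concern.** An event looked for each treatment day and dated when it appears is time-to-event data. Patients who leave early, or reach the last visit without OM, are censored. None of the named methods is built for that, so anyone following the section must turn onset into something else.

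- **As a continuous variable (onset day, t test):** only patients with an observed onset have a value. That subgroup is formed after randomisation and can differ by arm if ZYLGS works. The comparison is no longer intention to treat and cannot register patients in whom OM was prevented.
- **As a categorical variable (ever/never, chi-square):** the recorded dates are thrown away. A patient who left in week 1 without OM is either counted as a success or deleted.

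At stake is the answer on the first-named primary outcome. If ZYLGS patients leave earlier or more often and are counted as OM-free, the error favours the product. Unequal follow-up is plausible because the trial is open-label and the 70% intake rule can act in one arm only.

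**Working it through.** **1. The plan's own figure.** Inputs from the Sample size section: difference 0.9, SD 0.7, two-sided alpha 0.025, power 0.9. Normal formula: n per arm = 2(z₀.₉₈₇₅ + z₀.₉)²(SD/difference)² = 2(2.241 + 1.282)²(0.7/0.9)² = 15.02, so 16. The t-distribution version gives 16.35, so 17 per arm and 34 in all; 34/0.85 = 40. The figure reproduces, but it is sized on OM intensity. The article gives no onset rate, effect on onset or power for onset, and the abstract says 200 patients. Everything below therefore rests on assumptions and is shown at both 100 and 20 per arm.

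**2. Two models for onset.** Both have whole-day onset, 56 days of follow-up and dropout uniform over follow-up and unrelated to onset. The t test uses observed onsets only. Chi-square counts patients without observed onset as OM-free. All tests are two-sided at 0.05, with 500 to 1,000 simulated trials per cell.

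- Model A: Weibull shape 2, scale 17 days (median 17 × √ln 2 ≈ 14 days), plus a fraction never affected.
- Model B: Weibull shape 2.5, hazard ratio 0.6, control onset by week 8 of 70%, 90% or 99%.

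**3. Power with 15% dropout in both arms (t test / chi-square / log-rank, %).**

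| Scenario | 100 per arm | 20 per arm |
|---|---|---|
| A, prevention: never affected 30% vs 5% | 3–5 / 99 / 98–99 | 4 / 48 / 39 |
| A, delay: hazard ratio 0.6, 5% never in each arm | 91 / 5–6 / 67–69 | 29 / 4 / 21 |
| A, mixed: never 20% vs 5%, hazard ratio 0.8 | 24–27 / 82 / 93 | 10 / 24 / 32 |
| B, control onset 70% | 13 / 68 / 74 | 5 / 19 / 22 |
| B, control onset 90% | 29 / 67 / 89 | 10 / 18 / 28 |
| B, control onset 99% | 72 / 27 / 94 | 22 / 8 / 34 |

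Cross-check for B at 90%: the expected events are 100 × (0.824 + 0.675) ≈ 150. Schoenfeld: √(150/4) × |ln 0.6| − 1.96 = 6.12 × 0.511 − 1.96 = 1.17, so power is 0.88, against 0.89 simulated.

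The ranking depends on the assumptions. In model A's delay case, setting the never-affected fraction to zero raises log-rank from about 65% to 94%.

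**4. False positives, no true effect.** With equal dropout, model B gives 3–5% for chi-square and 4–6% for the t test. With dropout of 10% control and 30% ZYLGS (assumed), at 100 per arm:

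- Model A: t test 7%, chi-square 22%, log-rank 4–5.5%.
- Model B (70%, 90%, 99%): chi-square 25%, 44%, 59%; t test 6–8%; log-rank 4–6%.

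Hand check of the 44%: the observed OM proportions are 0.848 and 0.746. SE = √(0.848 × 0.152/100 + 0.746 × 0.254/100) = 0.0564; z = 0.102/0.0564 = 1.81; P = Φ(1.81 − 1.96) ≈ 0.44.

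At 20 per arm, model A gives chi-square 6–7%, t test 5%, log-rank 6%. The same hand formula for model B with SE multiplied by √5 gives about 9%, 13% and 16% for chi-square. This is rough with so few OM-free patients, but it shows that the 6–7% belongs to early onset. These rates apply when dropouts are coded OM-free. They do not carry over to deletion, where the objection is departure from ITT.

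**The case against.** The article never calls onset a time. Its stated aims are incidence, severity, prevention and management, and for incidence a chi-square test is natural. The chi-square sentence is generic and assigns no test to onset. A condensed article may leave event definitions and censoring rules to an analysis plan that is not shown.

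Part of this stands: the time-to-event reading is inferred from daily examination and recording of onset. But the section does allocate methods, giving the GEE to named outcomes and leaving t and chi-square tests for the rest. Even read as incidence, ever/never needs a rule for early dropouts.

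The log-rank test is also not best everywhere. The t test beats it clearly in model A's delay case, and chi-square edges it in pure prevention. At 20 per arm no test has adequate power. What remains is that each named test falls to about 5% power in one model A scenario at 100 per arm, while the log-rank does not.

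A reader might infer three stronger points that the documents do not support:

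- **Delay as a stated aim.** The article does not say so.
- **Unequal follow-up seriously biases both tests.** In these runs the t test stayed at 5–8%; the material inflation is in chi-square.
- **Multiplicity from testing onset twice.** Nothing says both tests will be run on onset.

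**Conclusion.** The point holds with moderate confidence. No named method suits a primary outcome that is observed daily and must be censored for some patients. The t test answers for a post-randomisation subgroup; the chi-square test ignores timing and mishandles dropouts.

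With equal dropout the cost is power and a partial answer, not false positives. With unequal dropout and dropouts coded OM-free, chi-square's false-positive rate can reach 22% or more at 100 per arm, and is much less inflated at 20 per arm. These sizes rest on assumed onset rates, effects and dropout, and on which of the two sample sizes applies. They also assume dropout unrelated to impending OM; if that fails, the log-rank test is affected too.

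**What to change.** Define onset as days from the first RT fraction to the first CTCAE grade 1 or higher OM, censored at the last OM examination. Analyse it in all randomised patients with Kaplan-Meier curves and a log-rank test, plus a Cox hazard ratio with 95% CI, both stratified by the randomisation factors (RT type and concurrent chemotherapy). Report cumulative incidence at the end of RT and at the two-week visit. State that weekend onsets are dated to the next examination, and that onsets after RT are known only to the interval before that visit.

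The cost is wording: the onset date is already recorded. The price in power is some loss against the t test in a pure-delay case and slightly less power than chi-square in a pure-prevention case. If the trial has 40 patients, the four strata average 10 each, so stratified estimates would be imprecise.

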#### Secondary outcomes

2.7.2

Secondary outcome measures will include nutritional status and health-related QoL.

The nutritional status evaluation indicators will include body weight, body mass index (BMI), albumin, hemoglobin and total lymphocyte count. Weight change will refer to weight loss during treatment. BMI is calculated by dividing body weight (kg) by the square of height (m). Weight change and BMI will be calculated before and after treatment. Blood indexes will be collected during the weekly routine blood and biochemical examinations.

The EORTC Core Quality of Life questionnaire (EORTC QLQ-C30) contains a series of HR-QoL issues related to a wide range of cancer patients. It has been translated into multiple languages and verified for multiple types of cancer, including HNC. It contains five functional scales (physical, role, cognitive, emotional and social), three symptom scales (fatigue, pain and nausea/vomiting), a global QoL scale, and six individual items (dyspnea, insomnia, appetite loss, constipation, diarrhea, and financial difficulties) [19]. The head and neck module (QLQ-H&N35) is a module used for evaluating the HR-QoL of HNC patients. It contains seven multi-item scales for evaluating pain symptoms, swallowing ability, senses (taste/olfaction), speech, social eating, social contact, and sexual behavior. It also includes six single-item scales to investigate the presence of symptoms related to teeth, mouth opening, dry mouth (xerostomia), sticky saliva, coughing, and feeling ill [20]. All scales of the EORTC QLQ-C30 and QLQ-H&N35 range from 0 to 100. A high score on the functional or global HR-QoL scale represents a relatively high/healthy functional level or global QoL, while a high score on the symptom scale represents the presence of symptoms or problems. Patients will complete both questionnaires before, at the 4th week of, and after RT treatment.

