## Discussion

3

RT-induced OM is a common problem and one of the major causes of pain and functional incapacity in HNC patients [3]. The present study aims to assess the effects of our TCM preparation on prevention and management of the pain, severity, and QoL of HNC patients with OM.

Many CHMs show significant improvements in side effects related to anti-cancer treatment, and TCM is the most common means of CIM in Taiwan. In a previous nationwide cohort study in Taiwan, 12.6% of patients with HNC used CIM, and the authors found that the number of TCM visits increased during multiple cancer treatments [22]. Another study reported the utilization of TCM to improve the survival outcome for HNC, and the results showed that longer use was associated with lower mortality [23]. We believe that it is possible to select formulae based on the pathogenesis of RT-induced OM and to use TCM theory to reduce the side effects of cancer treatment.

According to TCM theory, RT is a type of heat toxin that damages *qi* and yin and gradually affects the patient's physical strength [13]. Chemotherapy is also considered to aggravate a lack of *qi* [24], which can make wound healing more difficult [25]. ZYLGS provides an attractive therapeutic option for the prevention and management of OM, for the concept of using herbal components to clean the heat, replenish *qi* and nourish yin has been recorded in classical TCM books. Modern pharmacological research shows that *Rx. Scutellariae*, *Rx. Glycyrrhizae* and *Hb. Menthae Haplocalycis* have positive effects on oral epithelial damage. Their mechanism may be to inhibit oxidative stress and inflammation and thereby prevent bacterial dysbiosis [14]. *Hb. Dendrobii* can modulate macrophage activity via the NF-kB pathway and has been shown to act as an immune modulator to regulate gastrointestinal mucosal barrier function [26,27]. *Rx. Ophiopogonis* has been reported to stimulate lymphocyte proliferation *in vitro* [28]. Both are used for the benefit of *qi* and to promote body fluid production, according to TCM theory, and they are also reported to have the effects of cardiovascular protection, anti-inflammation and anti-cancer [27,29,30]. Although *in vitro* and *in vivo* studies have provided evidence supporting the purported effects of these ingredients of ZYLGS, we still perceive a need for a clinical trial to assess the efficacy of CHM formula in treating RT-induced OM.

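### All 28 EORTC scales and items are compared between arms under one p < 0.05 rule, with none named as key or exploratory, so isolated quality-of-life findings will be hard to interpret (minor, cheap to fix)

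*Protocol article*

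**What the plan says.** Section 2.8.2 (Data analyses) sets one general threshold: a two-sided p "< 0.05 will be considered significant". It then says that trends over time in "each scale/item of the EORTC QLQ-H&N35 and EORTC QLQ-C30, will be compared between groups", using generalized estimating equations (GEE).

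Section 2.7.2 (Secondary outcomes) gives the content of the two questionnaires. The QLQ-C30 has "five functional scales (physical, role, cognitive, emotional and social), three symptom scales (fatigue, pain and nausea/vomiting), a global QoL scale, and six individual items". Of the QLQ-H&N35 it says "It contains seven multi-item scales for evaluating pain symptoms" and other domains, and "It also includes six single-item scales to investigate the presence of symptoms". The same section lists five nutritional indicators: "body weight, body mass index (BMI), albumin, hemoglobin and total lymphocyte count".

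Nutrition and quality of life are both labelled secondary. The article does not rank them, name a key scale, give a testing order or call any of them exploratory. The Discussion includes quality of life among the study's purposes: the study "aims to assess the effects of our TCM preparation on prevention and management of the pain, severity, and QoL of HNC patients with OM".

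**The concern.** The article fixes two things at once: the full list of quality-of-life comparisons (every scale and item) and the threshold at which each may be called significant. With 28 comparisons, some will probably cross 0.05 by chance. Because no scale is named in advance, any one that does so can be reported as the quality-of-life result.

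The design makes this more than a formality. The trial is open-label and patients complete the questionnaires knowing their arm, so a chance difference on one subscale is easily read as a real benefit. What is at stake is the interpretation of the quality-of-life results, not the primary analysis of mucositis.

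**Working it through.** The article gives no error rate for the secondary outcomes, so there is no stated figure to reproduce. Sample size does not enter the calculation, because each test has its nominal level whatever the number of patients.

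**Inputs from the article**
- QLQ-C30 (section 2.7.2): 5 functional + 3 symptom + 1 global + 6 single items = 15.
- QLQ-H&N35 (section 2.7.2): 7 multi-item scales + 6 single items = 13.
- EORTC total: 15 + 13 = 28 comparisons, taken as one GEE group comparison per scale or item.
- Threshold (section 2.8.2): two-sided 0.05, which is 0.025 in the direction favouring ZYLGS.

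**Assumption not in the article**
- The correlation ρ between the test statistics is not given. I take it as equal for all pairs, with every scale oriented so that a positive statistic favours ZYLGS, and show 0 to 0.8.

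**Expected number of false significant results.** This does not depend on ρ: 28 × 0.05 = 1.4 in either direction, of which 28 × 0.025 = 0.7 favour ZYLGS.

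**Chance of at least one, independent tests**
- Either direction: 1 − 0.95^28 = 0.762.
- Favouring ZYLGS: 1 − 0.975^28 = 0.508.

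**Chance of at least one, correlated tests.** Given a shared standard normal factor u, the statistics are independent. Write a = (1.96 − √ρ·u)/√(1−ρ) and b = (−1.96 − √ρ·u)/√(1−ρ). Then, averaging over u:
- Either direction: 1 − E[(Φ(a) − Φ(b))^28].
- Favouring ZYLGS: 1 − E[Φ(a)^28].

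| ρ (assumed) | Either direction | Favouring ZYLGS |
|---|---|---|
| 0 | 76% | 51% |
| 0.3 | 64% | 34% |
| 0.5 | 49% | 25% |
| 0.7 | 33% | 17% |
| 0.8 | 25% | 12.5% |

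For comparison, one scale named in advance would carry 5% in either direction and 2.5% in favour of ZYLGS.

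**If the five nutritional indices are added.** Section 2.8.2 does not name nutrition, so this rests on applying its general sentence on t tests for continuous variables. The total becomes 28 + 5 = 33, and the expected count 33 × 0.05 = 1.65. At ρ = 0.5 the chance of at least one false significant result is 53% in either direction and 27% favouring ZYLGS. Under independence the figures are 82% and 57%.

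**The case against.** The strongest reply is that ranking or adjusting among secondary outcomes is commonly left to the statistical analysis plan, which is not shown, so its absence from an article is no error. The outcomes are already subordinated: section 2.7.1 names the primary outcomes, section 2.7.2 labels quality of life and nutrition secondary, and the sample size in section 2.8.1 rests on mucositis intensity alone. Nothing says that one significant EORTC scale would establish a benefit. Unadjusted secondary results read as supportive are also a defensible practice.

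Most of this stands and keeps the point minor. It does not remove it, because section 2.8.2 is not merely silent: it states a flat significance rule and applies it to every scale and item. An analysis plan with a hierarchy or an exploratory label would have to narrow that published rule.

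A reader might infer more than the article supports:
- *That a false benefit is as likely as not.* The 49% at ρ = 0.5 counts results in either direction, including those against ZYLGS. For 28 tests, a false benefit reaches 50% only if the correlation is about 0.01 or less, which is unlikely for subscales of the same questionnaires.
- *That the nutritional indices are stated to be tested at 0.05.* This is an inference from the general t-test sentence.
- *That repeated visits multiply the tests.* The GEE comparison is of trends over time, one longitudinal model per scale, not a test at each visit.
- *That the article promises strong evidence on quality of life.* Its closing claim in the Discussion concerns prophylaxis of mucositis.

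**Conclusion.** The point holds as a minor one about interpretation. The count of 28, the flat threshold and the lack of any named or exploratory scale all come directly from the article. The expected 1.4 false significant results under no effect follow from these alone. The probabilities also depend on the assumed correlation. At 0.5, the chance of at least one false significant result is about one in two in either direction and about one in four in favour of ZYLGS. Over correlations from 0 to 0.8 the ranges are 76% to 25% and 51% to 12.5%. Even the lowest figure for a false benefit is five times the 2.5% that a single scale named in advance would carry (12.5 / 2.5). The conclusion on the primary outcomes is unaffected.

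**What to change.** Add a short paragraph to section 2.8.2, settled before the quality-of-life data are analysed by arm:
- Name one or two key EORTC scales tied to oral mucositis, for example QLQ-H&N35 pain and swallowing. If two are named, state the order in which they are tested.
- Label all other EORTC scales and items, and the five nutritional indices, as exploratory. Report them as between-group estimates with 95% confidence intervals and no claim of significance.

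This needs no extra patients, data or procedures. The cost is that an isolated difference on a scale not named in advance can no longer be called significant.
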